**Methods:**

Barriers to exercise will initially be assessed in a qualitative study of newly diagnosed patients. Then, sixty newly diagnosed adult type 1 diabetes patients will be randomized to either conventional treatment or exercise, stratified on beta cell function and fitness. The exercise group will be encouraged to increase their level of activity to a minimum of 150 minutes of moderate to vigorous intensity exercise per week, aiming for 240 minutes per week of exercise for 12 months. Beta cell function will be measured by meal-stimulated C peptide. Primary outcomes are recruitment, adherence to exercise, loss to follow-up, and exercise levels in the non-intervention arm (contamination). The secondary outcome of the study is rate of loss of beta cell function.

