### Research goals

In order to test our hypothesis, we will initially undertake a qualitative study to identify barriers to the uptake and adherence to an intensive exercise program, and determine the most acceptable way to monitor exercise levels. We will then undertake a pilot RCT involving an exercise intervention in patients with recent onset T1DM in order to:

1) Determine the proportion and characteristics of patients with T1DM who would be willing to take part in an RCT of exercise (that is, recruitment rate).

2) Define the rates of exercise adherence to the intervention and participant drop-out. The unsupervised exercise program will aim to encourage patients to safely increase and maintain their exercise level to at least 150 minutes per week, and aiming for 240 minutes per week of vigorous intensity exercise. A minimum level of 150 minutes per week is recommended by major diabetes organizations [33,34]. However, to maximize the chances of seeing a benefit in beta cell function, patients will be encouraged to aim for 240 minutes per week.

3) Determine the rate of exercise uptake in the non-intervention arm (that is, intervention contamination). This issue is important because it has the potential to dilute trial effects, and adjustments for this will need to be made when calculating the sample size for a definitive trial.

4) Determine the rate of loss of beta cell function (potential effect size) in the intervention and control arm to enable the statistical power calculations for the subsequent definitive trial to be refined.

5) Determine (as a secondary outcome) whether the 12 months exercise intervention results in a significant preservation of beta cell function.

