### Planned sample size and analyses

A minimum of 30 patients per arm is considered sufficient to provide meaningful data to be obtained from this pilot study, but this will be reconsidered in the light of information gathered in phase 1. An initial recruitment rate of 30% is anticipated followed by a 90% adherence rate to the exercise schedule and a 15% drop-out rate. In order to complete the pilot study with a minimum of 30 patients, this means that 30/(0.85 × 0.9 × 0.3) = 130 patients will need to be approached initially.

With the varying sample sizes described above, estimates and 95% confidence intervals on recruitment rate, exercise adherence rate and drop-out rate will be:

Recruitment rate 30% (22% to 39%)

Adherence rate 90% (76% to 97%)

Drop-out rate 15% (5% to 30%)

Summary statistics (mean, standard deviation (SD), median, interquartile range (IQR), proportions) of demographic and primary outcome variables will be presented separately for intervention and control patients. Also, separately for intervention and control patients, change from baseline to 12 months in fitness related variables listed in Tables 3 and 4 will be estimated together with 95% confidence intervals. Trends over time in fitness related variables will be illustrated graphically. Variability in these changes will also be estimated in order to be able to estimate sample size requirements for a definitive trial. Comparison between intervention and control patients in change from baseline in fitness related variables will be made giving effect size estimates for the definitive trial. Association between fitness and demographic variables will be examined at a preliminary level using correlation analysis and chi-squared. A generalized linear model (GLM) will be used to get an initial impression of significance of differences between intervention and control groups in fitness related variables. Demographic variables and baseline fitness variable levels will be included as covariates. Further analysis will use non-linear mixed model analysis for outcome related fitness variables measures including the 19 sites as a random effect. Variation from site to site will then be used to further assist in the design of the definitive trial. The effect of demographic variables will also be investigated with mixed effect modeling.

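### The analysis section draws the definitive trial's variability and effect size from fitness variables, whereas the research goals require them for loss of beta cell function

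*Protocol article*

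**What the plan says.** In the protocol article, Research goals, item 4 reads: "Determine the rate of loss of beta cell function (potential effect size) in the intervention and control arm to enable the statistical power calculations". The calculations meant are those of the later full-scale study. Item 5 adds a test of whether 12 months of exercise preserves beta cell function. The abstract (Methods) states: "The secondary outcome of the study is rate of loss of beta cell function". It gives recruitment, adherence, loss to follow-up and contamination as the primary outcomes.

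Planned sample size and analyses takes a different variable. Separately by arm, "change from baseline to 12 months in fitness related variables listed in Tables 3 and 4 will be estimated together with 95% confidence intervals". The next use of those changes is: "Variability in these changes will also be estimated in order to be able to estimate sample size requirements for a definitive trial". The between-arm comparison of "change from baseline in fitness related variables will be made giving effect size estimates for the definitive trial". The GLM is to give a first impression of the "significance of differences between intervention and control groups in fitness related variables", and for that model "Demographic variables and baseline fitness variable levels will be included as covariates". Finally, "Further analysis will use non-linear mixed model analysis for outcome related fitness variables measures including the 19 sites as a random effect"; the site-to-site variation it yields is also meant to inform the definitive design.

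The Assessment section says that changes in the C peptide response to the mixed meal will show the effect of exercise on beta cell protection. It attaches no analysis to that statement.

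**The concern.** A sample size calculation needs the standard deviation and the plausible effect for the endpoint being tested. The abstract's discussion and the main Discussion both say that the definitive trial will be about beta cell preservation. The standard deviation and arm difference of a fitness measure, such as estimated VO2max, say nothing about the standard deviation and arm difference of C peptide. If the analysis section were followed to the letter, the quantities carried into the definitive design would belong to the wrong endpoint, and goals 4 and 5 would have no stated analysis behind them. An analysis plan written faithfully to this section would repeat the mismatch.

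**Working it through.** **1. The plan's own figures.** The number to approach is 30/(0.85 × 0.9 × 0.3) = 130.7, against 130 stated, so it reproduces (131 if rounded up). Exact 95% intervals:

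- Recruitment, 39/130: 22.3% to 38.7% (stated 22% to 39%).
- Adherence, 35/39: 75.8% to 97.1% (stated 76% to 97%).
- Drop-out: 4.8% to 30.3% with 5/35, or 5.7% to 29.8% with 6/40 (stated 5% to 30%).

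None of these involves fitness or C peptide, so the present point changes none of them.

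**2. What the pilot must deliver against what the section assigns.**

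| Item | Required by goals and abstract | Assigned in Planned sample size and analyses |
|---|---|---|
| Summary statistics | – | Demographic and primary outcome variables; C peptide is in neither set |
| Change to 12 months, per arm | Beta cell function (goal 4) | Fitness-related variables |
| Variability for the definitive sample size | Beta cell function (implied by the power purpose of goal 4) | The same fitness changes |
| Effect size for the definitive trial | Beta cell function (goal 4) | Fitness-related variables |
| Between-arm significance | Beta cell function (goal 5) | Fitness-related variables, by GLM |
| Covariates | – | Demographics and baseline fitness; baseline C peptide not named |
| Mixed model with site effect | – | Outcome-related fitness variables |

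**3. Whether the fitness phrase could include C peptide.** Table 3 lists the fitness test (estimated VO2max) and meal-stimulated C peptide as separate rows. Table 4 also separates them, at different visits: fitness at visits 3, 12 and 16, C peptide at visits 2, 11 and 17. The Randomization section lists 90-minute C peptide and fitness as two distinct minimization factors. The article's own usage therefore keeps the two apart.

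**4. Why the choice of variable matters (illustration, assumed values).** For two equal arms, n per arm = 2(1.96 + 0.84)²/d², where d is the arm difference divided by the standard deviation. At two-sided 5% and 80% power, d = 0.3, 0.4, 0.5, 0.6 and 0.8 need 175, 99, 63, 44 and 25 per arm. The article gives no d, alpha, power or C peptide standard deviation, so none of these is the right number. They show only that n depends strongly on d, and so on which endpoint d belongs to.

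**5. What the pilot could supply (illustration).** With 60 randomized and 15% drop-out, 60 × 0.85 = 51 complete, leaving 51 − 2 = 49 degrees of freedom. The 95% limits for a standard deviation, as multiples of its estimate, are √(49/70.2) = 0.84 and √(49/31.6) = 1.25. Squared, the implied n lies within 0.70 to 1.55 of its estimate. This is the precision of the pilot if C peptide is analysed; it does not measure the error.

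**6. Change score against baseline adjustment (illustration).** With equal variances at baseline and 12 months and correlation r, the ratio of adjusted to change-score variance is (1 − r²)/[2(1 − r)] = (1 + r)/2. That is 0.80 at r = 0.6 and 0.90 at r = 0.8, a saving of 10% to 20%. Both the correlations and the equal variances are assumptions. The second is doubtful for an outcome expected to fall, in patients selected for C peptide above 200 pmol/L.

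**The case against.** The best defence is that C peptide analysis is plainly intended. Goals 4 and 5, the Assessment section and the Discussion all commit to determining beta cell loss, and a condensed article may leave the estimator and model for a secondary outcome to a full protocol or analysis plan. That is correct, and a bare lack of modelling detail would be no finding. But the section is not silent: it states which variables supply the variability and effect size for the definitive trial, and they are not the ones in goal 4.

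The wording may also be loose. The fitness phrase is plural although each table has one fitness-test row, one sentence speaks of outcome-related fitness variables, and chi-squared is applied to measures that would mostly be continuous. The phrase may be careless shorthand for study outcomes in general. This lowers confidence about what was meant, but the tables and minimization factors count against the broad reading, and a reader cannot tell from the text.

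A reader might infer that the pilot will never analyse C peptide, or that its main aim fails. The documents do not support that. The primary outcomes concern feasibility and are unaffected, C peptide is collected at all three assessments, and its change is promised elsewhere. Nor is the use of raw change a separate error: the GLM already carries baseline fitness levels as covariates, so adjustment for baseline is part of the planned approach.

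**Conclusion.** The point holds as an internal contradiction. Planned sample size and analyses takes the change, variability, effect size and models that feed the definitive trial from fitness-related variables and does not name C peptide. Research goals 4 and 5 and the stated secondary outcome require these for beta cell function. The section should be corrected, since goals 4 and 5 have no stated analysis if it is followed literally.

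Its size cannot be given as a number. No stated figure changes, and no corrected sample size follows because the article contains no C peptide standard deviation. The range 0.70 to 1.55 and the 10% to 20% saving are illustrations and should not be cited as the cost of the error. The conclusion assumes only that fitness-related carries the meaning that Tables 3 and 4 and the minimization factors give it.

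**What to change.** In Planned sample size and analyses, state that:

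- change in meal-stimulated C peptide, using one pre-specified summary of the samples already scheduled, will be estimated per arm with a 95% confidence interval;
- the between-arm difference will be estimated with baseline C peptide as a covariate;
- the effect estimate with its interval, the residual standard deviation and the baseline to follow-up correlation will be the inputs to the definitive sample size;
- fitness variables are supportive analyses.

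The summary measure is for the sponsor to choose. An area under the curve over the sampling period is one option and the 90-minute value already used in minimization is another. Because the study team is not blinded, the choice should be fixed before outcome data are examined by arm.

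The cost is wording only. Meal tests are already scheduled at baseline, 6 and 12 months, so no visit, sample or recruitment figure changes.

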#### Randomization

Randomization will be done according to computer-generated allocation. Patients will be assigned, in a 1:1 ratio, to ‘usual care’ or ‘exercise intervention’. Allocations will remain concealed by the trial coordinator until the patients attends visit 4 when they will be randomized using on-line software. Randomization will be minimized by center, meal-stimulated 90-minute C peptide, and fitness. Due to the nature of the intervention, blinding of the study team to the randomization arm is not possible.

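### Allocation is minimized on center, 90-minute C peptide and fitness, but the GLM lists only fitness and demographics and no model names baseline C peptide: a modest loss of precision, not a bias

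*Protocol article*

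**What the plan says.** **Allocation.** The Randomization section of the protocol article sets a 1:1 ratio and three factors: "Randomization will be minimized by center, meal-stimulated 90-minute C peptide, and fitness". The Methods part of the abstract agrees on two of them, describing patients as "randomized to either conventional treatment or exercise, stratified on beta cell function and fitness".

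**Analysis.** Planned sample size and analyses first says that, within each arm, "change from baseline to 12 months in fitness related variables listed in Tables 3 and 4 will be estimated together with 95% confidence intervals". It then introduces a GLM to get an "initial impression of significance of differences between intervention and control groups in fitness related variables". The covariates follow: "Demographic variables and baseline fitness variable levels will be included as covariates". Center appears one step later: "Further analysis will use non-linear mixed model analysis for outcome related fitness variables measures including the 19 sites as a random effect".

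**The beta cell outcome.** Goal 5 under Research goals is: "Determine (as a secondary outcome) whether the 12 months exercise intervention results in a significant preservation of beta cell function". Goal 4 asks for the rate of beta cell loss in each arm, so that the power calculation for the definitive trial can be refined. The Assessment section says that the effect of exercise on the beta cell will be judged from changes in the C peptide response to the meal. No model is tied by name to this outcome.

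**The concern.** Of the three factors that steer allocation, fitness is in the GLM, center is only in the later mixed model, and 90-minute C peptide is in neither covariate list. Minimization forces the arms to be alike on C peptide. A model that ignores C peptide leaves whatever variance it explains in the error term, and takes no account of the balance that allocation has achieved. The reported standard error is then larger than it need be, and also larger than the true sampling spread of the estimate.

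Two things are at stake. The first is precision in a trial of 60 patients, whose Discussion names small size as a limitation. The second is the residual variance that the pilot hands to the definitive trial. If that variance is inflated, the next trial is planned larger than it needs to be, in a population that the Discussion says cannot be recruited in large numbers.

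**Working it through.** **Plan's own figure.** The article gives no SD, effect size or power for any between-arm model, so there is no figure on this point to reproduce. Its one sample-size calculation, 30/(0.85 × 0.9 × 0.3) = 130.7, agrees with the stated 130 but has no bearing here.

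**Factors set side by side.**

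| Minimization factor | GLM | Later mixed model |
|---|---|---|
| Center | not listed | random effect, 19 sites |
| 90-minute C peptide | not listed | not listed |
| Fitness | baseline levels as covariates | covariates not restated |

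**Fitness outcomes.** Inputs from the article: 30 per arm, 1:1 allocation, 19 centers, three factors, 15% drop-out (60 × 0.85 = 51 completers). Assumptions not in the article: C peptide and fitness each split in two for minimization; biased coin of 0.8; correlation of 0.6 between baseline fitness and outcome; correlation ρ between baseline C peptide and outcome, varied. With no treatment effect and 5,000 simulated trials per row, a linear model with arm and baseline fitness was fitted without and then with baseline C peptide (N = 60, nominal 5%):

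| ρ | Type I error without | Type I error with | Model SE without | Model SE with | Ratio |
|---|---|---|---|---|---|
| 0 | 5.1% | 5.3% | 0.2062 | 0.2070 | 1.00 |
| 0.1 | 5.4% | 5.6% | 0.2062 | 0.2054 | 1.00 |
| 0.2 | 4.1% | 4.4% | 0.2069 | 0.2011 | 1.03 |
| 0.3 | 4.4% | 4.7% | 0.2068 | 0.1926 | 1.07 |

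The simulation error on a 5% rate is √(0.05 × 0.95/5,000) = 0.3 percentage points. The formula √[(1 − 0.36)/(1 − 0.36 − ρ²)] gives √(0.64/0.55) = 1.08 at ρ = 0.3. With 51 completers the simulated ratio at ρ = 0.3 is 0.2242/0.2085 = 1.08. The loss for ρ up to 0.3 is therefore at most about 7–8% of the standard error.

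The conservatism can be seen at ρ = 0.3. The model without C peptide reports 0.2068, while its estimates actually vary with SD 0.1997, so the reported value is about 4% too large (0.2068/0.1997 = 1.04).

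At ρ = 0.5 and 0.7 the same simulation gives type I errors of 2.8% and 1.0% without C peptide, against 4.7% and 5.3% with it. Correlations of that size are plausible only for an outcome such as 12-month C peptide itself, and there the article plans change from baseline. Those two rows are not carried forward.

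**Change in C peptide.** Let σ² be the variance at each time point (assumed equal) and r the assumed correlation between baseline and 12 months.

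- Variance of the change score: 2σ²(1 − r)
- Residual variance after baseline adjustment: σ²(1 − r²)
- Variance ratio: 2/(1 + r); SE ratio: √[2/(1 + r)]

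| r | Variance ratio | SE ratio | Equivalent share of patients lost, (1 − r)/2 |
|---|---|---|---|
| 0.5 | 2/1.5 = 1.33 | 1.15 | 25% |
| 0.7 | 2/1.7 = 1.18 | 1.08 | 15% |

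The loss shrinks as r rises, because a change score already uses the baseline.

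**The case against.** The strongest objection is that the quoted covariate sentence belongs to a GLM for fitness related variables, and that nothing in the article says C peptide predicts fitness. That stands. A reader might infer that a strongly prognostic factor is being ignored in the named analysis; the document does not support this, and the loss there is small.

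A second objection concerns the C peptide outcome. The phrase about fitness related variables in Tables 3 and 4 can be read in two ways. If it excludes C peptide, the article states no model for that outcome, and a condensed article may leave that to a fuller document. If it includes C peptide, which both tables list, then baseline fitness levels by the same reading include baseline C peptide, and the omission largely disappears for that outcome. This stands in part: the C peptide figures above apply only if change is compared without baseline adjustment. Neither reading puts C peptide into the models for the other outcomes or center into the GLM, and the wording does not settle which reading is meant.

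A reader might also take the loss for C peptide from 1/√(1 − r²), which is 1.15 to 1.40 for r of 0.5 to 0.7, and conclude that 25% to 49% of the patients are thrown away. That formula compares baseline adjustment with an unadjusted 12-month value. The article plans change from baseline, so the comparator is √[2/(1 + r)].

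Finally, the GLM is meant only as a first impression, and the error is on the cautious side. Both are true. They limit the weight of the point but do not remove the mismatch.

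**Conclusion.** The mismatch is in the stated text: one of the three minimization factors is named in no between-arm model, and a second is missing from the GLM. The consequence is modest. In the linear model there is no bias and no inflated type I error; standard errors are somewhat too large and tests conservative.

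The loss is at most about 7–8% of the standard error for fitness outcomes if ρ is 0.3 or less. For change in C peptide without baseline adjustment, it is a factor of 1.15 (r = 0.5) to 1.08 (r = 0.7), with the variance overstated by 33% to 18%. All correlations, the equal variances and the details of the minimization are assumptions, because the article gives none of them.

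A reader might infer that the trial's main conclusions are affected. They are not: the primary outcomes are recruitment, adherence, loss to follow-up and contamination, and these models do not touch them. The point is still worth acting on, because goals 4 and 5 need an efficient C peptide comparison and a sound variance for the definitive trial.

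**What to change.** State that the between-arm models include all three minimization factors: baseline 90-minute C peptide and baseline fitness as continuous covariates, and center as a random effect. State also that the 12-month C peptide outcome is analyzed with this same baseline-adjusted model, and that its residual variance is the one carried into the sample size for the definitive trial.

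This takes a sentence or two. Baseline C peptide is already measured and already used for allocation, so no data are added; it costs one extra degree of freedom. Center as a random effect is already planned for the later model. The scale for C peptide and the choice of demographic covariates can be left to the trial team.

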## Methods and design

### Setting and recruitment

The study will take place across 19 NHS hospital Trusts in the UK: University Hospital Birmingham, Taunton and Somerset, University Hospitals Bristol, North Bristol, Gloucester Hospitals, Yeovil District Hospitals, East and North Hertfordshire, Mid Yorkshire Hospitals, Oxford University Hospitals, Worcestershire Acute Hospitals, George Eliot Hospital, The Dudley Group, Walsall Healthcare, The Royal Wolverhampton Hospitals, Heart of England, Sandwell and West Birmingham, Weston Area Health, Royal United Hospital Bath and Royal Devon and Exeter Hospital. Recruitment will focus on NHS hospital trusts as the vast majority of patients newly diagnosed with T1DM are referred to hospital for initiation of insulin.

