#### Post-randomization visits

In agreement with the local GPs and hospital doctors, the study team will undertake the ongoing diabetes management of all trial participants for the period of the trial. This is to ensure that similar guidelines for treatment intervention are maintained across all sites. Patients will be seen at baseline, 6 and 12 months by a doctor and any changes in treatment will be made according to strict guidelines, thus ensuring no bias between the two groups. All participants will have eight visits. Those patients randomized to the exercise arm will have a further five telephone consultations (see Table 4).

**Table 4 T4:** Visit overview

	**Pre-randomization**			**Randomization**	**Post-randomization**													
**Test/action**	**Visit 1**	**Visit 2**	**Visit 3**	**Visit 4 (wk 0)**	**Visit 5 (wk 2)**	**Visit 6 (wk 4)**	**Visit 7 (wk 8)**	**Visit 8 (wk 12)**	**Visit 9 (wk 16)**	**Visit 10 (wk 20)**	**Visit 11 (wk 24)**	**Visit 12 (wk 24)**	**Visit 13 (wk 30)**	**Visit 14 (wk 36)**	**Visit 15 (wk 42)**	**Visit 16 (wk 48)**	**Visit 17 (wk 48)**	**Visit 18 (wk 50)**
Clinical exam	x							x			x			x			x	
Questionnaires	x	x									x						x	
Activity monitor	x							x			x			x			x	
Non-fasting blood tests	x										x						x	
Fasting blood tests		x									x						x	
HbA1c	x							x			x			x			x	
Inflammatory markers		x									x						x	
Urine albumin/creatinine ratio		x									x						x	
Meal-stimulated C peptide		x									x						x	
Fitness test			x									x				x		
Nurse visit					x	X^a^	x	x	X^a^	x			X^a^	x	X^a^		X^a^	
Focus group feedback																		x

X: visit attended; wk: week. ^a^visit for exercise intervention arm only.

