**Figure 1 F1:**
[figure not shown]
Consort diagram describing flow of patients through study.

Participants will be assessed at baseline, 6 and 12 months. A schedule and details of assessments that will be carried out are given in Tables 3 and 4.

The clinical examination, and assessment of HbA1c, lipids, and renal and thyroid function constitute part of good clinical care and will inform the clinical management of the patient.

Downloads from the heart rate monitor and review of the exercise diaries will confirm and quantify the exercise being undertaken by patients in the exercise arm. Data from the activity monitors will enable us to assess whether we have managed to increase activity in both arms of the study.

Changes across the study in the C peptide response to a mixed meal will enable us to determine the effect that exercise has on beta cell protection.

Measurement of inflammatory markers will inform on the antiinflammatory effect of exercise. Measurement of islet antibodies will allow confirmation and sub-classification of T1DM for the final analysis of the data.

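### The mixed model for fitness is called non-linear with no non-linear form, and the site variance it would pass to the definitive trial is too imprecise with about three patients per site

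*Protocol article*

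**What the plan says.** The Planned sample size and analyses section sets out the fitness analyses in steps. It first estimates change from baseline to 12 months within each arm, and the variability of those changes, for later sample size work. It then compares the arms on change from baseline, and that comparison supplies the effect sizes for the definitive trial. A generalized linear model follows, with demographic variables and baseline fitness as covariates.

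Only after these does it specify "non-linear mixed model analysis for outcome related fitness variables measures including the 19 sites as a random effect". The next sentence gives the purpose: "Variation from site to site will then be used to further assist in the design of the definitive trial".

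The section gives no non-linear function and no reason for choosing a non-linear model. Site is the only random effect named, and the section does not say which visits enter the model.

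The size of the trial is fixed elsewhere. The abstract says that "sixty newly diagnosed adult type 1 diabetes patients will be randomized to either conventional treatment or exercise", and the Setting and recruitment section says "The study will take place across 19 NHS hospital Trusts in the UK". Under Assessment, "Participants will be assessed at baseline, 6 and 12 months". Table 4 places the fitness test before randomization, at week 24 and at week 48.

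**The concern.** There are two issues of different strength.

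The first holds on the text as written. The purpose of the pilot is to supply inputs for a definitive trial, and the article names site-to-site variation as one of them. A variance between 19 sites with about three patients each is very poorly determined. The same section attaches confidence intervals to the expected recruitment, adherence and drop-out rates but mentions no precision for this quantity. A designer who takes the point estimate could as easily get zero as a value several times too large.

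The second concerns how the model is specified. The non-linear label matches nothing else in the section. If the model takes one value per patient, there is no time course to bend. If it takes the scheduled fitness tests, there are three time points and no stated curve. If a generalized linear mixed model was meant, the label is wrong. And if two or more follow-up values per patient are analysed with nothing but a site effect, the correlation between values on the same patient is ignored and the arm comparison from this model looks more precise than it is.

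**Working it through.** **The section's own figure.** It states no site variance or ICC and no precision for either. Its one sample size calculation is 30/(0.85 × 0.9 × 0.3) = 130.7, given as 130. That reproduces and is not in dispute.

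**Inputs from the article.** 60 patients, 1:1 allocation, 19 sites, 15% drop-out, and two follow-up fitness tests (weeks 24 and 48).

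**Assumptions, because the article gives no values.** True site ICC of 0.05; within-patient correlation ρ of 0.5 to 0.8.

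**1. Patients per site.** 60/19 = 3.16. With 15% drop-out, 60 × 0.85 = 51 and 51/19 = 2.68.

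**2. Precision of the site ICC.** With k sites of m patients and true ICC r:

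SE = √[ 2(1 − r)²(1 + (m − 1)r)² / (m(m − 1)(k − 1)) ]

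- m = 3.16: √[2 × 0.9025 × 1.108² / (3.16 × 2.16 × 18)] = 0.134. Upper limit 0.05 + 1.96 × 0.134 = 0.31.
- m = 2.68: √[2 × 0.9025 × 1.084² / (2.68 × 1.68 × 18)] = 0.161. Upper limit 0.05 + 1.96 × 0.161 = 0.37.

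Both lower limits are negative and are set to 0. The standard error is about three times the assumed ICC.

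**3. Check by simulation** (one-way analysis-of-variance estimator, 20,000 trials per setting).

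| True ICC | Patients | Central 95% of estimates | Zero or negative |
|---|---|---|---|
| 0.05 | 60 | −0.19 to 0.32 | about 38% |
| 0.05 | 51 | −0.25 to 0.36 | about 40% |

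At a true ICC of 0 the upper 97.5% point is still 0.25 to 0.31. Uneven recruitment (sites of 1 to 12 patients, 60 in all) gives almost the same answer at 0.05: −0.21 to 0.33, with 38% zero or negative. The pilot could not tell no site effect from a large one.

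**4. Conditional check: several visits with site as the only random effect.** If m follow-up values per patient are treated as independent, the standard error of the average arm difference is understated by √(1 + (m − 1)ρ), and a nominal 95% interval covers 2Φ(1.96/factor) − 1.

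If the model adjusts for baseline, the correlation that remains under compound symmetry is (ρ − ρ²)/(1 − ρ²) = ρ/(1 + ρ). So 0.5 becomes 0.33 and 0.8 becomes 0.44.

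| Two follow-up fitness tests | Correlation | Factor | Coverage |
|---|---|---|---|
| No baseline adjustment | 0.5 to 0.8 | √1.5 = 1.22 to √1.8 = 1.34 | 89% to 86% |
| Baseline adjusted | 0.33 to 0.44 | √1.33 = 1.15 to √1.44 = 1.20 | 91% to 90% |

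If only the 12-month value or the change to 12 months is modelled, there is one row per patient and the factor is 1.

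**The case against.** The strongest reply is that the article does not say visits are treated as independent. It says that sites are included, not that nothing else is. It does not call this a repeated-measures model, and the same paragraph works with change to 12 months, which is one value per patient. A full analysis plan may well name a patient effect, and a condensed article commonly leaves that out. This stands: a reader might infer that repeated values are treated as independent, but the text does not establish it. The inflation factors therefore apply only if several visits enter with no patient-level term.

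A reader might also infer that the effect sizes passed to the definitive trial would be overconfident. The section does not support that. Those effect sizes come from the separate comparison of change from baseline, and the only output of the mixed model sent forward is the site variation.

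Larger factors could be quoted for the five time points in the "Activity monitor" row of Table 4. That would require activity data to count among the fitness variables of this model, which the section does not say, so they are left out.

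It would be too strong to say that 60 patients cannot yield a site variance, or that three time points rule out any non-linear model. The variance can be computed, and a mixed model pools over patients. The defects are imprecision in the first case and an unexplained label in the second.

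Finally, the article says only that site variation will further assist the design, the Discussion already concedes a small sample, and individual allocation minimized by center removes much of the between-site variation in level from the arm contrast. All of this limits the harm, and no error in a future sample size has been shown. It does not make an estimate with a standard error about three times its assumed true value useful for the purpose named.

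**Conclusion.** The point holds in limited form, as a minor one. The article commits to using a site variance that about three patients per site cannot determine with useful precision, and it labels the model non-linear without giving a form. The size rests on an assumed true ICC of 0.05. Simulated estimates centred on true values of 0 and 0.05 overlap almost completely, so the conclusion does not depend on that exact value.

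The understatement of standard errors, by a factor of 1.15 to 1.34 for two fitness visits, is conditional. It needs several follow-up values per patient in the model, no patient-level term, and a within-patient correlation of 0.5 to 0.8; where in the range it falls depends on whether baseline is adjusted for.

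Recruitment, adherence, loss to follow-up and contamination, which are the primary outcomes, do not depend on this model. Neither do the effect sizes from the change-from-baseline comparison.

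**What to change.** In the Planned sample size and analyses section:

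1. Replace the non-linear mixed model with a linear mixed model with site as a random effect. State which visits enter, and add a patient-level random intercept within site whenever more than one follow-up visit is analysed.
2. Adjust for the baseline value of the outcome and for the minimization factors, 90-minute C peptide and fitness; center is already covered by the site effect. C peptide is used in the allocation but is not among the covariates the section lists.
3. Report the site variance with its confidence interval, and carry a stated range of values, not the point estimate, into the design of the definitive trial.

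This takes a few sentences and needs no new data. The cost is wider reported intervals and a little more analysis work.
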